#### Baseline Data Capture

Regardless of the group assignment, all participants will undergo baseline data capture using their current passive energy storing and returning prosthesis. The study prosthetist will ensure proper fit and alignment of the prosthesis before any data collection. Once fit and alignment are confirmed, the participants will complete 3 surveys: an assessment of quality of life, the Prosthesis Evaluation Questionnaire (PEQ), and the PEQ Addendum. Then, pain, cognitive load, neurocognition, biomechanical gait analysis, and functional outcomes will be captured at baseline for all participants on their current passive energy storing and returning prosthesis.

#### Quality-of-Life Assessment

A single-item assessment will ask the participants to rate their quality of life over the past 4 weeks on a 100-mm visual analog scale.

#### Assessment With PEQ

The PEQ is a self-reported visual analog–style questionnaire for people with lower limb loss who use a prosthesis to evaluate the prosthesis and life with the prosthesis. The PEQ is organized into 9 domains that may be used independently to measure a specific domain of interest. Domains of utility, appearance, sounds, residual limb health, and ambulation will be used in this investigation. In addition, the PEQ contains items beyond the domains that can be evaluated individually, including questions on satisfaction, pain, and transfers that will be used in this study [41].

#### Assessment With PEQ Addendum

The PEQ Addendum asks 2 open-ended questions assessing any falls or stumbles that the participant may have experienced over the previous 4 weeks [42].

#### Pain Assessment

Participants will complete the Patient-Reported Outcomes Measurement Information System Pain Interference Scale 8a, which is a self-report survey that assesses the extent to which pain interferes with physical, psychosocial, cognitive, emotional, and recreational activities [43].

#### Neurocognitive and Cognitive Load for Prosthesis Use

Prosthesis use requires physical capabilities and the cognitive capacity to learn new techniques across different situations and environments. These skills include spatial organization, memory, attention, and visuospatial function [44]. Powered ankle-foot devices can be more complex than passive devices and may require certain levels of neurocognition and cognitive load for ambulation, especially for higher-level functional tasks. Diabetes and peripheral vascular disease, the most prevalent causes of lower limb loss, are linked to declining neurocognition [45,46]. Importantly, diminished neurocognitive function is not often observed until late in the rehabilitation process (well after prosthetic prescription) [47], which can result in the mismanaged use of staff and patient time and prosthetic resources. If certain levels of neurocognitive abilities correlate with successful prosthetic outcomes with the powered prosthesis, neurocognitive assessment (before prosthetic prescription) can potentially aid in the selection of appropriate candidates for advanced technology.

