### Study Objectives

The overarching goal of this investigation is to examine the roles of advanced prosthetic technology and a device-specific rehabilitative intervention in individuals with transfemoral limb loss. The central hypothesis is that powered plantarflexion, coupled with an evidence-based, device-specific PT intervention, will improve biomechanical outcomes, which will correlate with decreased pain and improved functional performance. The objectives of this investigation are as follows:

To examine the biomechanical and functional efficacy of a powered prosthesis compared with a passive prosthesis for individuals with transfemoral limb lossTo determine the effects of a powered prosthetic ankle-foot device and a PT intervention on lower extremity kinematic and kinetic patterns, functional efficacy, and pain in individuals with transfemoral limb lossTo develop preliminary rehabilitation guidelines for a powered ankle-foot device to minimize gait imbalances and maximize function, as well as to establish preliminary guidelines for powered ankle-foot prosthetic prescription

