### Planned Statistical Analysis for Cognitive Load and Neurocognitive Outcomes

Linear mixed-effects models will be performed to examine the differences between the ankle-foot devices on cognitive performance, walking speed, and subjective responses to attention. The parameters in the linear effects model will include prosthetic ankle-foot type, PT intervention, and participants. Ankle-foot type, PT intervention, and cognitive performance will be treated as fixed effects, whereas participants will be treated as random. The total number of errors and the error rates for the cognitive task will be calculated, and the mean error rate will be determined for each cognitive task performed by each participant. Repeated-measures ANOVA will be used to compare the error rates for the 3 cognitive tasks. Fisher least significant difference test will be used to make post hoc comparisons.

For the neurocognitive battery, Pearson correlation coefficients (pair-wise 2-tailed) will be calculated for all variables of interest. Stepwise multiple regression will be performed with the neurocognitive scores (Neurocognitive Index, composite memory, cognitive flexibility, and complex attention scores) as the dependent variable. The independent variables will comprise functional outcomes, pain, and gait biomechanics, including asymmetry index.

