## Discussion

### Expected Outcomes and Anticipated Principal Findings

After the completion of this research project, this investigation will have quantified the dependence of symmetrical lower limb gait biomechanics, physical function, and pain reduction on advanced prosthetic technology and device-specific rehabilitation. Furthermore, a device-specific treatment strategy designed to minimize impairments and maximize function will be evaluated. Finally, an objective measure of cognitive load and neurocognition to guide the prosthetic prescription of powered ankle-foot prostheses will be assessed. As such, the evidence-based outcomes obtained from this research investigation can be appropriately translated into clinical practice as well as drive the future of clinical care in this population.

VA provides care for veterans with limb loss of all generations, including the influx of service members with limb loss from the most recent conflicts [5]. Projected trends indicate that the overall number of individuals with limb loss will continue to increase dramatically, largely attributable to the aging population and the growing number of people with dysvascular disease and diabetes [1]. With this large population expected to grow, considerable resources will be required for rehabilitation and prosthetic services, driving limb loss care to become a high priority for VA. Effective outcomes-based clinical practice will be necessary to decrease long-term disabilities associated with prosthetic use and improve the quality of life. Therefore, it is the goal of this study to examine the effectiveness of a powered ankle-foot prosthesis and device-specific rehabilitation on gait biomechanics, performance, and pain in individuals with transfemoral limb loss. Results from this investigation will provide evidence-based outcomes that can be translated into successful strategies to minimize impairments and maximize function and may drive the evaluation of future advancements in prosthetic technology.

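### The neurocognitive analysis meant to inform powered-ankle prescription names no change from the passive foot and no neurocognition-by-device term, so it may find who walks well rather than who gains.

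*Protocol article*

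**What the plan says.** The Study Objectives section of the protocol article includes the aim "to establish preliminary guidelines for powered ankle-foot prosthetic prescription". The section on neurocognition and cognitive load for prosthesis use explains how the neurocognitive data would serve it: "If certain levels of neurocognitive abilities correlate with successful prosthetic outcomes with the powered prosthesis", assessment before prescription "can potentially aid in the selection of appropriate candidates for advanced technology". The discussion of expected outcomes repeats the aim: "an objective measure of cognitive load and neurocognition to guide the prosthetic prescription of powered ankle-foot prostheses will be assessed".

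The planned analysis for cognitive load and neurocognitive outcomes gives the battery two analyses:

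- **Correlations.** "For the neurocognitive battery, Pearson correlation coefficients (pair-wise 2-tailed) will be calculated for all variables of interest".
- **Regression.** "Stepwise multiple regression will be performed with the neurocognitive scores" as the dependent variable. For the other side of the equation: "The independent variables will comprise functional outcomes, pain, and gait biomechanics, including asymmetry index".

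The same section has a mixed model for cognitive performance, walking speed and attention ratings. There, "Ankle-foot type, PT intervention, and cognitive performance will be treated as fixed effects, whereas participants will be treated as random".

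Passive-foot outcomes are collected from everyone at baseline (Baseline Data Capture). The same outcomes are repeated on the powered foot at the final visit, together with the neurocognitive battery (Data Collection Visit 3).

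**The concern.** Deciding who should receive a device needs evidence about who does better on it than on the alternative. The stated condition looks only at outcomes on the powered foot. A person with better cognition may walk further, report less pain or show better gait on any foot. A correlation of that kind is a prognostic marker. Prescription needs a predictive one, meaning a characteristic that goes with a larger powered-versus-passive difference.

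The direction of the regression is a separate matter. Swapping the dependent and independent variables would not bring the passive foot into the comparison.

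At stake is a stated objective. A general link between cognition and mobility could be carried into preliminary prescription guidance as if it described benefit from the powered ankle.

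**Working it through.** **What each planned analysis can show**

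| Analysis (protocol article) | Passive foot enters? | Can show who gains? |
|---|---|---|
| Rationale for candidate selection | Not mentioned | No |
| Pearson correlations for the battery | Change scores not named | Not as written |
| Stepwise regression of neurocognitive scores | Ankle type and change not listed | Not as written |
| Mixed model with ankle type, PT and cognitive performance | Yes, as a fixed effect; no interaction stated | No |
| Powered versus passive models for gait, and comparisons for pain and function | Yes, on average | No; an average does not identify individuals |

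**Numerical check**

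The plan states no figure for the neurocognition-outcome correlation, so there is none to reproduce.

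Inputs from the article (Power Analysis and Sample Size Estimation; neurocognitive analysis section):
- N = 30, α = 0.05, two-tailed Pearson test.

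Assumed, because the documents do not give them:
- a true correlation r between neurocognition and outcome, the same on both feet;
- a passive-powered correlation w of 0.6 or 0.8 for the outcome;
- no device effect for the average participant, and none that depends on neurocognition.

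Critical value: t(0.975, 28 df) = 2.048, so |r| must exceed 2.048 / √(28 + 2.048²) = 0.361.

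Fisher approximation: power ≈ Φ(δ − 1.96) + Φ(−δ − 1.96), with δ = atanh(r) × √(30 − 3).
- r = 0.1: δ = 0.1003 × 5.196 = 0.521; power = 0.075 + 0.007 = 0.08.
- r = 0.2: δ = 0.2027 × 5.196 = 1.053; power = 0.182 + 0.001 = 0.18.

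Simulation with 40,000 trials per setting gives the following share of significant results:

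| r | Neurocognition vs powered value | vs passive value | vs powered minus passive |
|---|---|---|---|
| 0.1 | 8% | 8% | 5% |
| 0.2 | 19% (Fisher 18%) | 19% | 5% |
| 0.3 | 37% | 37% | 5% |
| 0.4 | 61% | 61% | 5% |
| 0.5 | 83% | 83% | 5% |
| 0.6 | 96% | 95% | 5% |

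The choice of w makes no material difference.

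The powered and passive columns agree to within simulation error. A correlation with powered-foot values therefore cannot separate general walking ability from device benefit. Subtracting 0.5 SD from every powered-foot value leaves its column unchanged, because a correlation ignores a constant shift.

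The last column shows the nominal 5% because cov(N, Y₁ − Y₀) = r − r = 0 under these assumptions (N is neurocognition; Y₁ and Y₀ are the powered and passive outcomes).

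**The case against.** Several objections carry weight.

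- **There is no decision rule.** A reader might infer that the protocol fixes a rule that would name candidates even if the device helped no one. The text does not support that. The sentence is a hedged rationale, no cutoff is given and the guidelines are preliminary. This stands.
- **Change is not excluded.** The correlations cover all variables of interest, and a successful outcome is not defined, so change scores could be meant. This stands as a possibility. However, neither analysis names change, and the rationale refers specifically to results with the powered prosthesis.
- **The device effect is tested elsewhere.** Powered versus passive is compared for gait, pain and function, so an absent average benefit would show there. That is true, but an average difference cannot show which participants benefit.
- **The question may be one of capability.** The section also says that powered devices may demand a certain level of cognition. For who can operate the device, performance on it is a fair outcome. This stands, and it is the right label for those correlations. It does not answer who gains over the passive foot.
- **The percentages are only Pearson power at assumed r.** Correct. The eligibility criteria exclude limiting cognitive deficits and set a mobility floor, so small r is plausible. That is why 0.1 and 0.2 are shown.
- **Change is not a clean device effect.** Everyone moves from passive at baseline to powered at weeks 4 and 8, so ankle type is fully aliased with time and practice. This stands. A reader might infer that prescription could rest on the change analysis alone, and the design does not allow that.

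**Conclusion.** The concern holds in a limited form. Followed as written, the neurocognitive correlations and regression can identify a prognostic marker, while the prescription objective needs evidence of who gains over the passive foot.

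The size depends on an unknown correlation. With no device effect, the chance that one test is significant runs from about 8% (r = 0.1) through 37% (r = 0.3) to 83% (r = 0.5). These figures illustrate the problem and do not estimate what this trial will find. The logical gap does not depend on them. The article does not show that prescription guidance will rest on these correlations alone, so the point is a recommended improvement to the analysis of a preliminary objective.

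**What to change.** For the prescription objective:

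1. Add a model of change in the same measure (powered at week 8 minus passive at baseline) on baseline neurocognition, with arm included. Equivalently, fit a baseline neurocognition-by-ankle-type interaction in the mixed model for those two visits. In that form, arm must be allowed to interact with ankle type.
2. Report correlations with powered-foot values as prognostic, that is, as describing ability to use the device and not who benefits from it.
3. State as a limitation that no arm stays on the passive foot. Including arm accounts for the PT difference, but change still carries time and practice effects. Keep prescription statements preliminary.

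The cost is wording and one added model. Baseline neurocognition and both sets of outcomes are already scheduled. The downside is that change carries measurement error from two visits, so fewer associations will reach significance with 30 participants.

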#### Cognitive Load Assessment

Cognitive load assessments will be performed at baseline using the passive energy storing and returning ankle-foot prosthesis. Before any cognitive load testing, a self-selected walking speed will be established via treadmill walking. The participants will be encouraged to walk unsupported on the treadmill, if possible. The treadmill console will be covered to prevent number distractions, and the participants will be reminded to hold their gaze straight ahead. To determine the self-selected speed, the participants will begin walking on the treadmill at a comfortable speed in the absence of any additional cognitive load. The treadmill will then be increased by 0.09 m/s every 10 seconds until the participant verbalizes their preferred speed. To avoid quick trigger responses, the speed will be increased by 0.18 m/s and then subsequently lowered by 0.04 m/s every 5 seconds until the participant verbalizes their preferred speed. If the final speed does not match the initial speed, this procedure will be repeated until the participant matches the preferred walking speed.

Cognitive load testing consists of five 1-minute standardized cognitive tasks: 1 serial subtraction task, 3 controlled oral word association tasks, and 1 category task. These tasks consist of auditory and verbal cognitive measures to simulate real-world conditions. Visual tasks will not be used to avoid measures that require reading while walking. The participants will complete each cognitive task while walking on a treadmill at the previously noted self-selected speed. The directions will be read to each participant to ensure protocol consistency. The number of correct answers will be determined for each 1-minute test using a digital voice recorder and paper recordings to ensure accurate documentation of the participants’ answers. The participants will complete a practice trial before each task initiation to ensure complete comprehension. The participants will also be allowed to rest between cognitive tests as needed. The cognitive tasks are as follows:

Serial subtraction: Serial subtraction is a mental arithmetic task [48]. The participants are given a random 3-digit number and asked to continually subtract 3 while they walk for 1 minute. The number of errors will be calculated. The participants are not penalized for multiple errors if 1 error was made; however, they continued sequentially thereafter.Controlled Oral Word Association Test: This measure consists of 3 tests that measure verbal phonemic fluency and other neuropsychologic domains [49]. The participants will be asked to list words beginning with a certain letter while walking for 1 minute. The test is then repeated for 2 other letters. The total number of unique words for each letter will be documented.Category Test: The participants are asked to list words belonging to a certain category within 1 minute (eg, fruits or parts of a car). Category naming has shown validity and reliability [50]. The total number of unique words for each category will be documented.

After each cognitive load test, the participants will be asked to rate on a 0 to 10 scale (with 0 being “none” and 10 being “a great deal”) their focus on walking, their focus on thinking of words or subtracting numbers, and their focus on distractions. This will provide information on the subjective experience of cognitive load.

#### Neurocognitive Assessment

Following the cognitive load assessment, the participants will take an electronic neurocognitive battery (CNS Vital Signs) [51]. The computerized neurocognitive assessment measures 5 domains (memory, psychomotor speed, reaction time, complex attention, and cognitive flexibility), is designed to be administered serially, and has demonstrated good test-retest reliability. The neurocognitive assessment consists of the following 7 tests:

Verbal memory: the participants are instructed to remember 15 words that are displayed 1 at a time every 2 seconds. The target words are then randomly mixed with 15 new words. The participants are instructed to press the space bar when a target word is displayed. This test is repeated at the end of the assessment with the same 15 target words randomly mixed with 15 new nontarget words.Visual memory: the participants are instructed to remember 15 geometric shapes that are shown 1 at a time every 2 seconds. The shapes are then randomly mixed with 15 new nontarget shapes. The participants are instructed to press the space bar when they identify a target shape. This test is repeated at the end of the neurocognitive assessment period.Finger tapping: the participants are instructed to tap the space bar with their right index finger as quickly as possible during the 10-second test. The test is then repeated with the left index finger.Symbol Digit Coding: this test consists of 8 digit-symbol pairs, followed by a list of digits. The participants are instructed to serially type numbers that correspond to the symbols during the 120-second test.Stroop test: in part 1 of the Stroop test, the participants are randomly shown the words “GREEN,” “YELLOW,” “RED,” and “BLUE.” These words are printed in black. The participants are instructed to press the space bar when they see one of these words. In part 2, the same words appear on the screen but are printed in different colors. The participant is instructed to press the space bar when the color presented matches the word (eg, the word “RED” is printed in red). In part 3, the same words are presented on the screen in different colors. The participants are then instructed to press the space bar when the color presented does not match the word (eg, the word “RED” is printed in green).Shifting Attention: in this test, 3 figures appear on the screen. There is a single figure at the top of the screen (either a circle or a square). At the bottom of the screen, 2 figures are presented (both a square and a circle). The figures are randomly mixed to be either red or blue. The participant is then instructed to match one of the corresponding bottom figures with the top figure by shape or color. However, the rules for matching by shape or color change at random. This test occurs for 90 seconds.Continuous performance test: during a 5-minute period, the participants are asked to press the spacebar when the letter *B* appears on the screen. The participants are further instructed not to respond to any other letters. The letters are presented at random.

#### Biomechanical Gait Analysis

Gait analyses will be performed at the biomechanics laboratories at VANYHHS, WRNMMC, and JAHVH. The VANYHHS laboratory is a 133-m^2^ space comprising an 11-camera motion capture system (Qualisys, Inc) with 4 multiaxis force platforms (AMTI, Inc). At WRNMMC, the biomechanics laboratory is an 167-m^2^ space comprising an 18-camera motion capture system (Qualisys, Inc) and 6 multiaxis force platforms (AMTI Inc). At JAHVH, the motion capture laboratory is a 74-m^2^ space equipped with a 12-camera motion capture system (Vicon Inc) and 4 multiaxis force platforms (AMTI Inc). All 3 systems track the positions of passive reflective markers at a rate of 120 Hz, and force platforms sample ground reaction forces at a rate of 1200 Hz. Visual3D software (C-Motion Inc) will be used for the analysis of 3D motion capture data.

All laboratories in this investigation will follow recommendations provided by an interlab reliability study that was conducted between gait laboratories at the 3 military treatment facilities [52]. Specifically, all sites will use identical marker sets, identical anatomical segment definitions, and a single examiner at each site to conduct postprocessing of the respective data to reduce potential variability between the laboratories.

For all participants, biomechanical gait analysis will be performed at baseline using their prescribed energy storing and returning prostheses. All kinematic and kinetic biomechanical measures will be captured using an identical 6-degrees-of-freedom marker set. A custom, full-body passive reflective marker set will be placed on each participant, which tracks each segment independently, allowing for the accurate measurement of movements. As previously described [53], 78 markers will be placed or digitized on the head, trunk, pelvis, and extremities. Marker placements for the prosthetic limb will be matched to those of the intact leg or placed on the centers of rotation of the prosthetic ankle-foot and knee devices. The cluster technique will be used to minimize the surface-to-bone displacements for the thigh, shank, and upper arm–mounted markers [54]. Tracking clusters will be placed bilaterally on the thigh, the tibial crest, and the upper arm. Functional joints, adapted from Schwartz and Rozumalski [55], will also be calculated for the intact ankle and knee as well as bilaterally for the hips.

During each experimental session, the participants will separately walk at 3 speeds across an instrumented walkway until 5 acceptable trials for each foot at each speed are completed. Trials will be considered acceptable when a foot makes full contact with a force platform. Because kinetic outcome measures are speed-dependent, the participants will ambulate at 3 controlled speeds: 0.7, 1.0, and 1.3 m/s. These speeds were selected to represent a slow, moderate, and fast walking speed, respectively, for individuals with transfemoral limb loss. The order of speeds will be randomized for each data collection visit. Auditory feedback will be provided to the participant by the study team to ensure that all participants walk at the targeted speed (−5% to +5%). The main purpose of this session is to collect joint motion, force, torque, and power data at each walking speed. The ranges of motion; speeds and accelerations; and hip, knee, and ankle joint moments of force and generated and absorbed powers will be computed using inverse dynamics methods. Temporal-spatial parameters will also be recorded.

The reflective marker positions will be digitized using motion tracking software. A 15-segment rigid body model (head, trunk, pelvis, bilateral upper and lower arms, hands, thighs, shanks, and feet) will be created based on the skin-mounted markers and functional joints. Local coordinate systems for each segment will be defined using the International Society of Biomechanics recommendations [56,57]. The data of 5 acceptable walking trials at each speed will be processed using Visual3D. Marker data will be filtered with a 6 Hz Butterworth low-pass filter. Raw analog data will be filtered using a second-order low-pass Butterworth filter with a 25-Hz cutoff frequency. Visual3D will be used to calculate temporal-spatial values, walking speed, and lower extremity kinematics and kinetics. Inverse dynamic analysis will be applied to the kinematics of the biomechanical model and to the location, magnitude, and direction of ground reaction forces acting on the foot to calculate lower extremity joint torques and powers, including ankle, knee, and hip power of the biological and prosthetic limb over the stance phase, as well as the frontal plane knee moments for the unaffected leg.

